## Abstract

Lumbar disc degeneration (LDD) and low back pain (LBP) are two conditions that are closely related. Several studies have shown *Cutibacterium acnes* colonization of degenerated discs, but whether and how these finding correlates with LBP is unknown. A prospective study was planned to identify molecules present in lumbar intervertebral discs (LLIVD) colonized by *C*. *acnes* in patients with LDD and LBP and correlate them with their clinical, radiological, and demographic profiles. The clinical manifestations, risk factors, and demographic characteristics of participants undergoing surgical microdiscectomy will be tracked. Samples will be isolated and pathogens found in LLIVD will be characterized phenotypically and genotypically. Whole genome sequencing (WGS) of isolated species will be used to phylotype and detect genes associated with virulence, resistance, and oxidative stress. Multiomic analyses of LLIVD colonized and non-colonized will be carried out to explain not only the pathogen’s role in LDD, but also its involvement in the pathophysiology of LBP. This study was approved by the Institutional Review Board (CAAE 50077521.0.0000.5258). All patients who agree to participate in the study will sign an informed consent form. Regardless of the study’s findings, the results will be published in a peer-reviewed medical journal. Trials registration number NCT05090553; pre-results.

## Introduction

LBP is a common complaint in the general population, and its incidence is about five times higher in patients with LDD and Modic endplate changes [1, 2]. The link between these findings and the isolation of low virulence pathogens in LIVD has already been described in several studies, generating a lot of interest in the topic and promoting the bacterial hypothesis of LDD [3–14].

Albert et al. reported 46% of positive cultures for anaerobes in 61 patients undergoing lumbar discectomy, of which 80% had Modic type 1 changes [15]. Other studies corroborate these findings, with high identification rates for *Cutibacterium acnes*, an anaerobic and aerotolerant pathogen that is bacillus-shaped, stained by the Gram method, pleomorphic, non-spore-forming, and a biofilm producer [11, 16–20]. Rollason et al. isolated strains of this bacterium from the LIVD of 64 patients, revealing the presence of genotypic profiles distinct from those found in the skin, suggesting that specific variants would be related to LBP [21].

Other authors believe that the presence of this pathogen in the LIVD of asymptomatic patients is due to contamination of the specimens during sampling and/or sample treatment in the laboratory environment. Carricajo et al. found positive cultures for *C*. *acnes* in only 3.4% of the discs from 54 patients, defending the possibility of contamination [22]. Rigal et al. also analyzed LIVD from 313 patients who underwent video-assisted retroperitoneal discectomy, with positive cultures for only six patients [23].

These marked divergences in microbiological results cast doubt on the bacterial hypothesis of LDD and, consequently, raise questions about the possibility of anaerobic pathogens acting as triggers or amplifiers of LBP. Urquhart et al. conducted a systematic review of the literature on the subject and concluded that there is evidence correlating the *C*. *acnes* isolation with Modic type 1 changes and LBP, but there is a lack of studies producing substantial and irrefutable evidence [24].

Despite the fact that considerable effort has already been expended in determining the presence of *C*. *acnes* in LIVD, there are still no standard isolation protocols for this pathogen from this clinical specimen. Furthermore, prior to the preparation of this manuscript, studies have shown no consistency in the collection and analysis techniques used, making comparison and reproducibility of results difficult.

Aware of this reality, Astur et al. proposed a protocol for a cohort study to identify *C*. *acnes* from intervertebral discs [25]. Although valid, the initiative has two significant limitations that should be highlighted. First, after collecting clinical specimens, their immediate inoculation in a liquid medium is not foreseen in the operating room, which increases the contact time of the samples with the aerobic environment and reduces the chances of microorganism recovery even with culture-specific techniques. Second, the authors also highlight sonication (ultrasound waves to release bacteria from the biofilm of surgical prostheses) of specimens for subsequent inoculation in automated blood culture vials; however, this technique was originally described for pathogen recovery from orthopedic prostheses rather than biological tissue [26] and, because the sonication parameters used are not clear (time, power, and frequency), the reproduction of results by other authors and the validation of this protocol is compromised.

Specific microbiological identification techniques, such as immediate inoculation of specimens in liquid culture medium while still in the operating room, vortex for sessile cell recovery, incubation time extension in an anaerobic atmosphere with replication every 72 h, and the use of Matrix-Assisted Laser Desorption Ionization Time of Flight Mass spectrometry—MALDI-TOF MS (Bruker Coorporation), and multiplex-touchdown PCR are strategies that assure reliable results regarding the presence of bacteria in intervertebral discs [27, 28], but they do not explain the pathways through which these microorganisms would participate in LDD and/or LBP.

Once LIVD colonization by *C*. *acnes* is confirmed using microbiological techniques, in the absence of clinical signs of infection, the main challenge is to understand the implications of this finding for homeostasis of that microenvironment. Rajasekaran et al. showed strong evidence of LIVD colonization by *C*. *acnes* using rDNA-16s PCR and proteomic analyses [29]. These authors discovered not only host defense proteins, but also proteins associated with bacterial viability and proliferation. Although these findings have demonstrated the active presence of *C*. *acnes* in intervertebral discs, definitively ruling out the possibility of contamination, they do not necessarily reflect the activity of the expressed proteins, which may remain inactive and without interference in pain-generating pathways and/or the inflammatory response.

In this context, the combined use of proteomic and metabolomic techniques to analyze LIVD colonized by *C*. *acnes* would be more appropriate in order to assess the subclinical consequences of the colonization by this pathogen [30]. These techniques have already been used successfully to define molecular signatures in other clinical settings [31–34], especially in chronic pain [35–40], and can also provide integrative information on cell function at the molecular level about the role of *C*. *acnes* in LDD and LBP [41–44].

## Hypotheses and objectives

Our hypothesis is that LDD and LBP are related to LIVD colonization by *C*. *acnes*.

The primary goal of this study is to determine the incidence of LIVD colonization by low virulent pathogens using specific sampling and culture techniques, as well as phenotypic and genotypic techniques for microbiological characterization.

Other objectives of the study include: 1- assessing the possibility of clinical specimen contamination in positive cultures; 2- establishing a correlation between the presence of the pathogen and the clinical and radiological profile (Modic type 1 changes) of the study participants; 3- to outline a phylotypic profile of the most isolated *C*. *acnes* strains by bacterial WGS; and 4- identify a molecular profile for LDD and LBP in patients with positive cultures for *C*. *acnes* through proteomic and metabolomic techniques.

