#### Inclusion criteria

The inclusion criteria for the study will be participants aged between 18 and 65 years; both sexes; complaint of low back pain lasting more than 3 months; magnetic resonance imaging findings of lumbar disc degeneration (LDD) performed less than 6 months before inclusion in the study; indication for open surgical treatment with isolated microdiscectomy or associated with lumbar arthrodesis; failure of conservative treatment for at least 6 weeks and/or progressive neurological deficit; agreement to follow all phases of the clinical investigation, having signed the informed consent form (ICF) for participation in the study.

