### Host multiomic characteristics

Proteomic and metabolomic techniques will be used to examine disc and plasma samples. The comparison of the group of molecules found in disc and plasma samples may contribute to the quantitative and qualitative identification of profiles using peripheral blood that are associated with the presence of the pathogen in the intervertebral disc. After processing the multiomic raw data using proper bioinformatics tools, statistical techniques will be applied to analyze them against the clinical–radiological and microbiological profiles of the participants. We expect to provide a molecular signature relating the presence of *C*. *acnes*, LDD and LBP.

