### Imaging studies

Imaging studies include 1.5 T magnetic resonance imaging. The tests must be dated no later than 6 months prior to the participant’s inclusion in the study. Any of the following changes will be considered disc degeneration: disc protrusion, extrusion, or sequestration; reduced disc intensity; annular ruptures; Schmorl’s nodes (Depressions on the surface of the vertebral bodies identified on MRI scans that result from the pressure exerted by the intervertebral discs on the endplates, causing intervertebral disc tissue herniation and displacement into the adjacent vertebral bodies); Modic changes; and/or loss of disc height.

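### Low back pain and disc degeneration are entry criteria for everyone, so the study can relate colonization to their severity but not to having either condition, and the hypothesis and objective 4 should say so

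*Protocol article*

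**What the plan says.** Under Hypotheses and objectives, the protocol article states: "Our hypothesis is that LDD and LBP are related to LIVD colonization by" *C. acnes*. Objective 4 in the same section is to "identify a molecular profile for LDD and LBP in patients with positive cultures for" *C. acnes*, by proteomics and metabolomics. Host multiomic characteristics adds: "We expect to provide a molecular signature relating the presence of" *C. acnes*, LDD and LBP.

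Inclusion criteria require of everyone both "complaint of low back pain lasting more than 3 months" and "magnetic resonance imaging findings of lumbar disc degeneration (LDD) performed less than 6 months before inclusion in the study". Imaging studies defines degeneration broadly: "Any of the following changes will be considered disc degeneration: disc protrusion, extrusion, or sequestration", among several other findings, any one of which is enough. The Primary outcome is confined to patients who have both conditions.

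The groups named under Modic changes are colonized and non-colonized. Metabolomics uses disc fragments with and without an isolate. Under Sampling, the skin, muscle–ligament and blood specimens come from the same patients as the discs.

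The article also collects measures that vary between participants: Pfirrmann grade, Modic type 1, and VNS, ODI and EQ-5D at recruitment and at 1, 3 and 6 months. Host multiomic characteristics and the regression paragraph closing Statistical analysis methodology plan to relate the omic data, and colonization, to clinical and radiological variables.

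**The concern.** The hypothesis and objective 4 are worded about the conditions themselves, and the entry criteria remove all variation in whether a participant has them. A factor that is the same in every participant cannot be shown to be associated with anything in that sample.

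The interpretation of the omic work is at stake. In a colonized versus non-colonized comparison, molecules shared by all painful degenerated discs cancel out, and what remains reflects colonization. Under the heading of objective 4, that remainder could be presented as markers of degeneration or pain. The Justifications section expects the molecular profile to affect clinical management, so the label matters. It would also lend support to the bacterial hypothesis that the study sets out to examine.

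**Working it through.** **1. The article's own figure.** Sample size calculation gives a minimum of 96 with 95% confidence and a 10% margin of error. No expected proportion is stated, so I assume the worst case, p = 0.5:

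n = z² p(1 − p)/d² = 1.96² × 0.25/0.10² = 96.04.

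This reproduces 96. The recruitment target of 120 agrees with 96/(1 − 0.20) = 120, under an assumed loss of 20%. The size is set by the precision of one proportion; no contrast on LDD or LBP enters it.

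**2. Presence of LDD or LBP against colonization.** The article fixes no expected colonization share. Its Introduction cites 46% (anaerobes) and 3.4% (*C. acnes*) from earlier series; I use these only as an illustrative range, with n = 96.

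| Assumed share | LDD and LBP present: colonized / not | LDD or LBP absent: colonized / not | Odds ratio |
|---|---|---|---|
| 46% | 44 / 52 | 0 / 0 | (44 × 0)/(52 × 0), undefined |
| 3.4% | 3 / 93 | 0 / 0 | (3 × 0)/(93 × 0), undefined |

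The second row stays empty at any sample size. The enlargement and mid-study revision allowed under Sample size calculation cannot fill it.

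**3. The omic contrast.** Both arms of the colonized versus non-colonized comparison come from patients with LDD and LBP, so the arms differ by design only in colonization. Read literally, objective 4 is narrower still: it looks within culture-positive patients, all of whom have both conditions.

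**4. What can be estimated.** Severity varies. For a continuous score compared between colonized and non-colonized patients, with a two-sided 5% level, 80% power, n = 96, equal SDs and one value per patient, the detectable difference in SD units is

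(1.96 + 0.84) × √(1/a + 1/b),

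where a and b are the group sizes.

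| Assumed share | a vs b | Detectable difference |
|---|---|---|
| 46% | 44 vs 52 | 0.57 SD |
| 20% | 19 vs 77 | 0.72 SD |
| 10% | 10 vs 86 | 0.94 SD |
| 3.4% | 3 vs 93 | 1.64 SD |

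All shares are assumptions, and with three colonized patients the normal approximation is rough. A severity association is therefore estimable, with sensitivity that depends heavily on the colonization share.

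**The case against.** The strongest reply is that the hypothesis says only that the conditions are related to colonization; it does not specify presence versus absence. Nobody plans the two-by-two table above, and the Primary outcome openly restricts the question to patients with both conditions. Host multiomic characteristics and the regression paragraph already plan to relate omic data and colonization to clinical and radiological variables. Pfirrmann grade, VNS, ODI, EQ-5D and Modic type 1 supply variation, and Secondary outcomes defines a 30% rise in pain in the first postoperative month, which can also differ between participants. Objective 2 covers the clinical as well as the radiological profile.

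Much of this stands. A reader might infer that colonized versus non-colonized is the only contrast in the study, that nothing about LDD or LBP can be learned from the samples, or that the hypothesis stays untested whatever the result. The documents do not support those readings, because within-cohort associations with severity are measurable and broadly planned.

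The reply does not rescue the wording. Association with severity among surgical patients is a different quantity from association with having the condition. Neither the hypothesis nor objective 4 mentions severity, and objective 2 names only Modic type 1 for the radiological part. That no presence-versus-absence table is planned confirms the gap between what is claimed and what is designed. Nor is this a detail that a statistical analysis plan could supply: the hypothesis, objectives and entry criteria are all stated, and no analysis can create a comparator that the criteria exclude.

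**Conclusion.** The point holds in this limited form. The design cannot estimate whether having LDD or LBP is related to *C. acnes* colonization, at any sample size. Its colonized versus non-colonized omic comparison describes colonization among patients with symptomatic degenerated discs and should not be called a molecular profile for LDD and LBP. Severity associations within the cohort are estimable: at n = 96 the detectable difference runs from 0.57 SD to 1.64 SD as the assumed colonization share falls from 46% to 3.4%.

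This rests on the entry criteria being applied as written and on no unaffected comparator being sampled. LDD is required per patient, so an operated level without any listed MRI change is conceivable. No such comparison is planned, and that patient would still have LBP. The primary outcome and its sample size are unaffected.

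**What to change.** - Restate the hypothesis and objective 4, for example: among patients operated on for chronic LBP with LDD, colonization and the disc and blood molecular profile are associated with degree of degeneration (Pfirrmann grade of the sampled disc, Modic type 1) and with pain intensity (baseline VNS).
- In the regression paragraph of Statistical analysis methodology, name Pfirrmann grade and baseline VNS as the ordinal and continuous variables to be related to colonization and to the omic data.
- Report the colonized versus non-colonized omic contrast separately, as a profile of colonization among these patients.
- Limit the molecular signature expected under Host multiomic characteristics to association within the cohort.

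The cost is a narrower claim, some rewording, and analyses of variables already collected. No patients or samples are added. Keeping the broader claim would instead require a comparator without LDD or without LBP, which the present design does not include.

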### Justifications

Colonization of LIVD by *C*. *acnes* in patients with LDD supports the bacterial hypothesis of LBP [4, 8, 29, 45–47]. The determination of a molecular profile for these patients will not only contribute to a better understanding of the pathophysiological basis of LBP associated with LDD [41–43], but it will also positively interfere in the clinical management of this common condition, rationalizing its treatment and optimizing its costs.

Previously studies looked at small groups of patients and did not follow standardized sampling and analysis methods [15, 24, 48, 49]. This makes it difficult to value these findings and while they do suggest a correlation between *C*. *acnes* and LBP, the evidence is insufficient to explain how this bacterium could be involved in the process of LIVD degeneration and generation/amplification of LBP.

This is the first protocol to investigate the role of *C*. *acnes* in LIVD degeneration, combining isolation with culture techniques, phenotypic and genotypic characterization techniques; and genomic, proteomic, and metabolomic techniques. In addition, the protocol proposes the clinical–radiological characterization of the participants, blinding the researchers and controlling confounding variables, and following appropriate selection criteria and statistical planning to obtain significant results.

## Methods and analysis

This study protocol is registered with the Research Ethics Committee (REC) [CAAE: 50077521.0.0000.5258] of the Gaffrée and Guinle University Hospital (HUGG) and at *Clinicaltrials*.*gov* under NCT05090553 (https://clinicaltrials.gov/ct2/results?term=NCT05090553).

### Ethics and dissemination

The protocol will follow the ethical standards of the HUGG REC. All patients whose biological materials will be analyzed will be well-informed of the research objectives and will sign ICF, agreeing with the availability of samples for further laboratory analysis.

### Study design

This analytical study will be performed at a single location (Spine Surgery Center of São Matheus Hospital (HSM) in collaboration with the Gaffrée Guinle University Hospital (HUGG) and Anaerobic Biology Laboratory of Paulo de Góes Microbiology Institute of the Universidade Federal do Rio de Janeiro (UFRJ).

The analyses will be performed sequentially, according to the surgical procedures carried out on the selected participants, taking 6 months after for their recruitment and ending 6 months after the surgical treatment of the last patient. Data from participants will be collected using a form designed specifically for this study.

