### Patient and public involvement

Participant eligibility will be evaluated by the study researchers through a clinical interview and imaging exams evaluation, according to the participants’ interest and availability to participate in the study. If the patient agrees to take part in the study, the predetermined selection criteria will be used to evaluate them. The researchers will explain the details of the study and conduct a joint reading of the ICF. Questions about the study objectives, risks and benefits, stages, and research confidentiality will be answered. A patient will only participate upon signing the ICF at this stage of the research. A copy of this document will be given to the participant, another to the responsible researcher, and a third will be attached to the medical record. After signing the consent form, the patient will undergo an evaluation for demographic and clinical data collection and the forms developed for this purpose will be completed. If the patient is unable to read and sign the written consent form, researchers will verbally explain the study details and the patient will orally provide consent in the presence of a witness who will sign the consent form. The recruitment of participants will take place over a 6-month period, until 120 individuals are included, aiming at a minimum number of 96 collections.

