### Laboratory analysis

#### Cultures

The skin swabs will be opened only in a laboratory setting. Samples will be seeded on blood agar plates (5% defibrinated sheep blood; blood agar base, 40 g/L; agar, 5 g/L) and anaerobic blood agar (5% defibrinated sheep blood; blood agar base, 40 g/L; agar, 5 g/L; hemin, 10 mL/L; menadione, 5 drops/L. After sowing in solid media, the swab will be inoculated in thioglycolate medium, where it will remain for 14 days. One of the plates will be incubated in a capnophilic atmosphere (5% to 10% CO_2_), while the other will be incubated in strict anaerobiosis (atmosphere containing 10% CO_2_,10% H_2_, and 80% N_2_) using an anaerobic chamber or Glove Box (Coy Labs^®^, USA).

The plates will be read after 24 h of incubation and, in case of growth, the colonies will be identified. In the absence of growth, they will be incubated again, and a new reading will be performed after 72 h. The thioglycolate vials containing skin swabs will be kept in a bacteriological incubator (35°C to 37°C) for 14 days. In a laboratory setting, the tubes containing disc fragments and muscle–ligament tissue will undergo vortexing (Even EVX2800-BI^®^, Brazil) for 15 s. All tubes will be kept in a bacteriological incubator (35°C to 37°C) and, after 24 h, the first subculture will be carried out using a 100 μL bacteriological loop. An aliquot of the thioglycolate will be taken and plated on blood agar and anaerobic blood agar. The first plate will be incubated in a capnophilic atmosphere and the second in strict anaerobiosis using an anaerobic chamber or Glove Box (Coy Labs^®^, USA). The plates will be read after 24 h and the colonies will be identified in case of growth. In the absence of growth, they will be incubated again, and a new reading will be performed after 72 h. The same procedure will be used for all thioglycolate vials (totaling six vials for each level approached). Thioglycolate tubes containing the clinical specimens will be kept in an oven for 14 days. Subcultures will be carried out after 72 h and always every 3 days, with the last subculture being carried out on the 14^th^ day of incubation in the same solid culture medium and atmospheres used in the first 24 h.

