#### Quality control of culture media

Sterile saline solution at 0.9% will be used to control the sterility of the culture medium and *Pseudomonas aeruginosa* ATCC 27853 and *Bacteroides fragilis* ATCC 25285 strains to evaluate the recovery capacity of facultative microorganisms and strict anaerobes. Each new batch of culture medium prepared will undergo this quality control.

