#### Proteomics

In this study, proteomics approaches will apply gel-free and in-gel protein digestion by using sodium dodecyl sulfate polyacrylamide gel electrophoresis (SDS-PAGE) technique [2].

Thioglycolate culture mediums will be centrifuged, and the sediment obtained will be washed in phosphate buffer and centrifuged again. The sediment will be dissolved in a lysis solution containing 8 M urea, 2% 3-[(3-cholamidopropyl) dimethylammonio]-1-propanesulfonate, and 40 mM Tris (hydroxymethyl) aminomethane. This lysis will be complemented with the use of glass beads under a Bead Beater agitation (Biospec Product^®^, USA) (3 × 20 s with intervals of 20 s) followed by cooling for 5 min on an ice bath, as described by Shah et al. [55]. Protein concentration will be measured and 20 μg will be used for both the gel and solution techniques.

The SDS-PAGE -based technique will be used to evaluate the profile of the proteins present in the extract. Proteins will be removed from the gel with a sterile scalpel, eluted, and trypsinized (proteolic digestion) for further analysis through mass spectrometry. In the solution technique, the obtained extract will be trypsinized for further analysis through mass spectrometer. Regardless of the technique used, a nano-Liquid Chromatography coupled to a high-resolution mass spectrometer (nLC-HRMS) will be used.

After analysis by both techniques, the raw data (.*raw*) will be converted into a mascot general file (.*mgf*) using the Mascot Distiller software version 2.8.0, and proteins will be identified using protein banks referring to *C*. *acnes* and eukaryotes (humans), both created using the NCBI as a *fasta* extension. After this identification, the data will be validated using the Scaffold software version 5 for the same databases. Two biological replicas will be made for both the gel and solution technique. The Interactivenn.net [http://www.interactivenn.net/index.html] [56] and STRING version 11 software [57] will be used for comparative analysis and functional interaction of proteins, respectively.

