#### Metabolomics

The metabolomic analysis in this study will use intervertebral disc fragments with and without isolated *C*. *acnes*. The tubes containing the disc fragments in thioglycolate liquid culture medium will be centrifuged and the sediment will be transferred to 2 mL flat-bottom polypropylene tubes containing a titanium bead (one per tube). The liquid content of these tubes will be evaporated by centrifugation with the CentriVap SpeedVac apparatus (Labconco Corporation^®^, USA) and then weighed to determine the dry weight. The tubes will then have 500 μL of MS Grade (Fluka) acetonitrile added followed by Bead Beater agitation (Biospec Product^®^, USA) (4 x 30 s). When all the material has been dissolved, the tubes will be centrifuged, and the supernatant will be stored at −80°C in new sterile tubes. To identify the metabolites, the material will be injected into a high-resolution mass spectrometer (UHPLC Q-TOF MS/MS). The data obtained will be analyzed in the Metaboanalyst 5.0 database [https://www.metaboanalyst.ca/] and its functions and interactions in the STRING software version 11 [57].

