## Statistical planning

### Sample size calculation

Considering the main outcome proposed, the identification of disc colonization by *C*. *acnes*, the minimum sample size (*n*) for the population of interest will be 96 participants, according to the calculation described by Medronho et al., [59] using a confidence interval of 95% and a maximum margin of error of 10%.

The ideal sample size for analysis of secondary outcomes will depend on the incidence of the main outcome. If it is too low, an increase in the number of patients included will be performed with the inclusion of more blocks of participants. In order to have a more accurate dimension, the sample size calculation will be revised as soon as we reach half of the initially planned sample size.

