### Statistical analysis methodology

The database will be analyzed using the SPSS software, version 22.0, and R software, version 4.0.2. Descriptive analysis will be performed by charts and descriptive statistics. The inferential analysis will consider a maximum significance level of 5%. The chi-square test or Fisher’s exact test will be used for inferential analysis of the distributions of categorical variables. The odds ratio (OR) will be the measure used to estimate risk. The OR’s significance will be evaluated by the OR’s asymptotic confidence interval. The hypothesis of normality will be verified by the Kolmogorov–Smirnov and Shapiro–Wilk tests. Student’s t-test or Mann-Whitney test will be used in the comparison of the two independent groups. More than two independent groups will be compared by the ANOVA or by the Kruskal–Wallis test. Two repeated measures in different assessments will be compared by the paired Student’s t-test or by the Wilcoxon’s signed-rank test. More than two repeated measures will be compared by the ANOVA for repeated measures, or by the Friedman’s test.

The identification of an optimal cutoff point for the marker associated with an outcome will be established through the analysis of the receiver operating characteristic (ROC) curve. The performance will be evaluated by the area under the ROC curve (AUC), and the significance of the AUC will be evaluated by the test that judges the null hypothesis that AUC is equal to 0.5. In addition to the significance test, the asymptotic confidence interval for the AUC will be obtained.

Analysis of the association between two quantitative variables will be visualized by scatter plots and quantified by the Pearson correlation coefficient, in the case of normal distributions, or by the Spearman’s correlation coefficient, if normal distribution is not verified in at least one of the variables. The significance of the correlation coefficient will be evaluated by the correlation coefficient test.

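### Omic samples processed in surgical order leave medium lot, and possibly instrument run, following calendar time; balancing runs and recording lot is a cheap protection against a false colonization signature

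*Protocol article*

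**What the plan says.** Under Study design, the protocol article states: "The analyses will be performed sequentially, according to the surgical procedures carried out on the selected participants". The sentence then gives the recruitment and follow-up period. It makes no exception for the multiomic work.

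Four other sections bear on this:

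- **Cultures.** Colonization is read from thioglycolate tubes over two weeks: "Thioglycolate tubes containing the clinical specimens will be kept in an oven for 14 days".
- **Proteomics and Metabolomics.** The disc material comes from thioglycolate cultures. For proteomics, "Thioglycolate culture mediums will be centrifuged, and the sediment obtained will be washed in phosphate buffer and centrifuged again". For metabolomics, the tubes holding the disc fragments are centrifuged and the sediment is extracted.
- **Quality control of culture media.** Medium is prepared in successive batches: "Each new batch of culture medium prepared will undergo this quality control". The check covers sterility, and recovery of *Pseudomonas aeruginosa* and *Bacteroides fragilis*.
- **Storage.** For metabolomics, "the supernatant will be stored at −80°C in new sterile tubes" before injection. Serum is also kept at −80°C (Sampling). The Proteomics section states no frozen storage.

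Instrument run order is not given. The list under Confounding variables contains patient characteristics only.

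**The concern.** One reagent, the thioglycolate medium, both helps to decide whether a disc is called colonized and forms part of the material measured by the omic methods. If a lot is contaminated, or lets *C. acnes* grow more readily, it can raise the share of discs called colonized and also change the chemical background of those samples. The batch check may not reveal a difference in *C. acnes* recovery, because neither control strain is *C. acnes*.

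Instrument drift between runs acts in a similar way if runs follow surgical order and positivity changes over time. Molecules that differ only between lots or runs could then be reported as the molecular signature of colonization, which is one of the study's stated objectives. Even with no such link, run-to-run variance that is left in the error term blurs true differences.

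**Working it through.** **The plan's own figure.** The sample size rests on the precision of one proportion: n = z²p(1−p)/d². With z = 1.96, d = 0.10 and p = 0.5 (not stated, but the value that gives the result), n = 3.8416 × 0.25 / 0.01 = 96.04, so 96 is reproduced. The recruitment target fits it: "The recruitment of participants will take place over a 6-month period, until 120 individuals are included, aiming at a minimum number of 96 collections", and 120 × 0.80 = 96. This fixes the number of samples used below, taking one disc sample per participant.

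**Inputs the document does not give (assumed).** Number of lots and runs, size of their effects, and how far positivity varies between them. The Introduction cites culture positivity from 3.4% (*C. acnes*) to 46% (any anaerobe). Tests are two-sided at 5%; the plan gives the 5% but not the sidedness.

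**Check 1: run effects.** There are 96 discs in 8 runs of 12, with about 46% colonized and no true group difference. Each molecule is a run effect plus residual, with total variance 1 and a run share of 20% or 40%. The logit of the colonized share varies between runs with a given SD. Groups are compared by an unadjusted t-test, with 400 null molecules per simulated study. Ranges cover repeated sets of simulations (150 or 400 studies per setting).

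| SD of logit positivity between runs | Mean false-positive rate, 20% run variance | Mean false-positive rate, 40% run variance |
|---|---|---|
| 0 (stable) | about 5% | about 5% |
| 0.5 (moderate) | about 6% | about 8% |
| 1.0 (strong) | about 9% | 12–13% |

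For SD 0.5–1.0, one study in ten has at least 9–20% of its null molecules at p < 0.05, depending on the setting. With 20% colonized the pattern is the same, with means of about 6–12%. If the groups are balanced within runs, the unadjusted rate is 2–3%, which is conservative until run enters the model.

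**Check 2: medium lots.** There are 96 samples in equal consecutive lots, with a lot SD equal to the within-lot SD (so lot is half of the total variance). Each scenario has 4,000 replicates.

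| Positivity over lots | Unadjusted error: 4 lots | 6 lots | 12 lots |
|---|---|---|---|
| 30% throughout | 5.3% | 5.1% | 5.4% |
| 20% rising to 40% | 8.8% | 7.5% | 5.2% |
| 10% rising to 50% | 20% | 13% | 9% |
| One lot at 80%, the others at 20% | – | 26% | – |

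With lot fitted as a fixed effect, the error returns to 4–6% in all these scenarios. If lot and status coincide completely, no within-lot comparison exists and adjustment cannot help.

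**Gain from blocking without any drift.** Removing a run share of 20–40% from the error variance is worth 1/(1−0.2) = 1.25 to 1/(1−0.4) = 1.67 times the number of discs, that is 25–67% more. This follows directly from the assumed share.

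**Limit on balancing.** At 3.4% positivity, 96 × 0.034 ≈ 3 discs are positive, which cannot be spread over 8 runs. At 46%, 96 × 0.46 ≈ 44, and they can.

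**The case against.** The strongest reply is that the Study design sentence describes the flow of the study. It goes on to the recruitment and follow-up period and never mentions instruments. Frozen storage of serum and metabolomic extracts suggests that mass spectrometry could be done later in any order. Run order and batch terms are also details that an article may leave to a fuller document. This stands in part: the tie between instrument run and calendar time is conditional. But the sentence covers the analyses without exception, so an order is stated, and the tie of medium lot to calendar time does not depend on how instruments are scheduled.

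A reader might infer that sequential processing in itself confounds run and lot with colonization. The documents do not support that. Surgical order is set before status is known, nothing says positivity will drift or that the groups are handled separately, and chance imbalance between runs is not bias. At stable positivity the simulations show about 5%.

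Two further objections also stand. Randomizing runs cannot balance lot, because fragments enter the medium in the operating room. And the plan already guards against contamination, through batch sterility checks, skin and muscle–ligament samples, and a stated objective to assess it. These guards lower the chance of a contaminated lot. They do not address a lot that merely recovers *C. acnes* better, or instrument drift.

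**Conclusion.** This is a cheap improvement to a stated order of work, and no bias has been shown. Taken literally, the Study design section makes medium lot, and possibly instrument run, follow calendar time. The harm requires positivity to vary by lot or over time. If it does, the mean false-positive rate is roughly 6–13% in place of 5%, given run effects of 20–40% of variance and logit SDs of 0.5–1.0. The larger assumed lot effect gives up to 26% with one deviant lot in six. All these sizes rest on assumed numbers of runs and lots, effect sizes and drift, and none comes from the documents. The stronger statement, that these effects are already linked to colonization status, does not hold.

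**What to change.** 1. Amend the Study design sentence so that surgical order applies to collection and culture only.
2. Hold the serum and metabolomic extracts already kept at −80°C until culture status is known. Do the same for the proteomic extracts if they can be stored; the article does not say.
3. Assign samples to mass-spectrometry runs at random, balanced on colonization status within runs as far as the number of positives allows.
4. Record medium lot and run for every sample. In each omic comparison, include run as a block and lot as a covariate.
5. Report positivity by lot. Lot cannot be balanced because it is set at collection, and adjusting for it does not correct discs wrongly called positive because of a contaminated lot.

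The cost is that omic results arrive later and that someone in the laboratory prepares a run list. No extra samples are needed.
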